#### Outcomes instruments for caregivers

The caregiver assessment includes the positive parenting, positive involvement and corporal punishment subscales of the Alabama Parenting Questionnaire [72], the PHQ-9 [53] and additional questions covering household members, migration background, contextual stressors, adverse life events, welfare benefits, income, debt, household expenditure, aspirations and beliefs for index child/self [47], Multi-Dimensional Poverty Index, adapted for each country [30, 48, 73], and social security.

#### Assessment of costs and cost consequences of the intervention

As part of the objective to test trial procedures, we will also conduct an exploratory economic evaluation of all three newly developed interventions, in which we will examine costs and possible offsets of delivering the intervention in the three country settings. In each country, we will collect information from key ALIVE team members about resource inputs that go into the delivery of the interventions, and into training and supervision of the facilitators. Information sources that we will draw from include project administration data such as manuals, attendance and budget sheets.

An adapted version of the Client Service Receipt Inventory, developed by Beecham and Knapp [54], will also be included in the adolescent and caregiver assessments to assess use and cost of physical and mental health services and wider support and advice (e.g. with debt, career). Caregivers will report for themselves and the index adolescent participant at all follow-up assessments, while adolescent participants will also report for themselves at the 12-month post-baseline assessment.

### Procedures

#### Data collection for pilot cRCT

Refer to Fig. 1 for the SPIRIT schedule of enrolment, interventions and assessments. Adolescents and caregivers will be assessed on four occasions to assess sensitivity to change of measures and to assess a change in incidence of depression and/or anxiety, as well as all other outcomes, from baseline (T0) to post intervention (T1), 12 months post-baseline (T2), and 18 months post-baseline (T3). Baseline data collection for adolescents was ideally completed 1–4 weeks before the intervention started and initiated immediately after the screening questionnaire (MMAPP) and enrolment. If baseline data for caregivers were not already collected as part of the Phase 1 cross-sectional survey, baseline data were also collected 1–4 weeks before the intervention started. Data collection for both adolescents and caregivers at T1, T2 and T3 will be conducted within a 3-week window from the scheduled post-baseline timepoint. Please refer to Fig. 2 for an overview of the timeline for step 1 and step 2 enrolment, interventions and assessments of participants.

**Fig. 1 Fig1:**
[figure not shown]
SPIRIT schedule of enrolment, interventions and assessments for participants

**Fig. 2 Fig2:**
[figure not shown]
Study timeline for enrolment, intervention and assessments of participants

Data collection for adolescents takes place in a closed venue (e.g. classroom) or private room either on school premises, or within their homes, depending on participants’ preferences. First, the self-report instruments and neuropsychological tasks are administered and the physiological measures collected by research assistants. In South Africa, the self-report instruments are self-administered in small groups, with the help of the research assistants. In Colombia and Nepal, they are administered individually to each participant, though participants may be asked to self-administer several key sensitive items to avoid social desirability. The administration of the instruments for the primary caregiver takes place either on school premises, or in the participants’ homes, reverting to remote data collection only if needed. The assessments should take approximately 60–90 min (for adolescents) and 60 min (for caregivers) to complete.

Data are collected electronically using Android tablets linked to the ODK platform (https://getodk.org/); regular checks of data values are performed to ensure data quality. All data collection is conducted in Spanish (Colombia), Nepali (Nepal) and English (South Africa). In South Africa, the research is taking place in the Western Cape province, where English, Afrikaans and isiXhosa are the most frequently spoken languages. Nevertheless, previous research has shown that adolescents prefer completing questionnaires or interviews in English, even if their first language is isiXhosa or Afrikaans. For caregivers in South Africa, however, instruments are administered in English, isiXhosa or Afrikaans, depending on the caregivers’ preferences.

#### Masking

All lead investigators and research assistants (except research assistants in South Africa) will remain masked to allocation status of participants enrolled into the study. A Standard Operating Procedure (SOP) has been put in place with details on who can know what, on what scripts can be used when communicating about the study and what strategies are in place to prevent and assess unmasking. To maintain masking, separate research assistants will conduct the qualitative and quantitative assessments, research assistants will have separate offices to intervention facilitators, and the level of (un)masking will be assessed at the end of each of the four assessments.

#### Contamination and drifting

Participants will not be given information about the content of the intervention provided in the other trial arms at any point during the study. However, to assess the extent of contamination across trial arms, participants in all four arms will be asked several structured questions at each of the measurement points (excluding baseline) about the extent to which they shared information and materials about the intervention received with others in the community (intervention arms), and whether they have heard of information or materials about the intervention from others (all four arms). This information will be used descriptively to assess the level of contamination and drifting. As part of the inclusion criteria, we have included sufficient distance between schools (> 1 km) to reduce the risk of contamination.

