**Feasibility of the study procedures**				
Feasibility of randomisation	Difference in participant recruitment rate between arms	1. > 60% participants agree to be (i) re-screened to determine eligibility for the pilot, or (ii) enrolled into the pilot (when second screening for pilot does not take place) 2. > 30% difference in recruitment rate between arms	1. > 60% participants agree to be (i) re-screened to determine eligibility for the pilot, or (ii) enrolled into the pilot (when second screening for pilot does not take place) 2. 20–30% difference in recruitment rate between arms	1. > 60% participants agree to be (i) re-screened to determine eligibility for the pilot, or (ii) enrolled into the pilot (when second screening for pilot does not take place) 2. < 20% difference in recruitment rate between arms
Feasibility of masking research assistants	Self-report questions at the end of each assessment	> 50% guess correct arm	35–50% guess correct arm	< 35% guess correct arm
Feasibility of data collection	Proportion of missing items on the GAD-7 and PHQ-A items at 18 month follow-up	> 20% missing	10–20% missing	< 10% missing
Feasibility of retention	Proportion of recruited adolescents lost to follow-up (LTFU) at 18-month follow-up	> 30% LTFU	20–30% LTFU	< 20% LTFU

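### In Colombia and Nepal the contamination questions at T1 to T3 can tell masked research assistants who is in an active arm, and the masking guess taken at the end of the assessment would then partly measure that disclosure

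*Protocol article*

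**What the plan says.** **Who is masked.** The Masking section states: "All lead investigators and research assistants (except research assistants in South Africa) will remain masked to allocation status". The masked assessors are therefore those in Colombia and Nepal.

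**How data are collected there.** Data collection for pilot cRCT says of the self-report instruments: "In Colombia and Nepal, they are administered individually to each participant". Some sensitive questions may be handed over for self-completion. They are not listed, and the contamination items are not named among them.

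**The contamination questions.** Under Contamination and drifting, "participants in all four arms will be asked several structured questions at each of the measurement points (excluding baseline"). Follow-up runs from baseline "to post intervention (T1), 12 months post-baseline (T2), and 18 months post-baseline (T3"), so the questions fall at T1, T2 and T3. There are two sets:
- Active arms only are asked "about the extent to which they shared information and materials about the intervention received with others in the community (intervention arms").
- Everyone is asked "whether they have heard of information or materials about the intervention from others (all four arms").

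**The masking check.** The Masking section says "the level of (un)masking will be assessed at the end of each of the four assessments". Table 7 gives the indicator as "Self-report questions at the end of each assessment" and scores correct guesses of the arm as red above 50%, amber at 35–50% and green below 35%.

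**The concern.** Asking a pupil whether they passed on material from the intervention they received shows the interviewer that the pupil received one. The answer may also show which one. If the person asking is meant to be masked and records a guess of the arm when the session ends, that guess reflects what the questionnaire has just shown.

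Two things are at stake. First, masking is one of the pilot's progression criteria. A reading that mixes disclosure by the contamination items with any other loss of masking does not tell the full trial whether masking held while outcomes were being collected. Second, knowledge gained at T1 can be carried into T2 and T3, when the PHQ-A and GAD-7 (the intended primary outcomes of the full trial) are collected again.

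**Working it through.** **Step 1. Who could be asking?** The Masking section describes two groups of research assistants, quantitative and qualitative. The qualitative team interviews within 4 weeks of the end of the intervention. Its purposive sample per country includes 18 adolescents from the active arms and 3 from the control arm. It reaches neither all participants nor T2 and T3. No third group is described, so on the article's text the quantitative research assistants ask the contamination questions. This is an inference: the sentence is in the passive voice and names no asker.

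**Step 2. Does the article see the hazard elsewhere?** Yes. Data collection for qualitative interviews separates that team because such interviews would show which arm a family is in. The contamination items also concern the intervention received, and the article describes no matching safeguard for them.

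**Step 3. Effect on the guess.** The Table 7 limits come without a derivation, so there is no stated figure to reproduce. The inputs are four arms in a 1:1:1:1 ratio (Randomisation into study arms; Sample size), taken as equal in the realised sample. Let q be the share of participants whose status is disclosed to the assessor. Anyone not disclosed is guessed correctly 25% of the time.

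*Only active versus control disclosed.* Control participants (25%) are then always guessed correctly, and active ones (75%) one time in three:

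P(correct) = q × (0.25 × 1 + 0.75 × 1/3) + (1 − q) × 0.25 = 0.25 + 0.25q

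*Exact arm disclosed through the answers:*

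P(correct) = q + (1 − q) × 0.25 = 0.25 + 0.75q

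| q | Active/control only | Exact arm |
|---|---|---|
| 0 | 25% | 25% |
| 0.25 | 31% | 44% |
| 0.40 | 35% | 55% |
| 0.50 | 38% | 63% |
| 1 | 50% | 100% |

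The 35% green limit is reached at q = 0.10/0.25 = 40% if only active versus control is disclosed, and at q = 0.10/0.75 = 13% if the exact arm is. The 50% amber/red border is reached at q = 100% and at q = 0.25/0.75 = 33% respectively.

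**Step 4. Carry-over within a school.** The school is the unit of randomisation, so one disclosure informs the assessor about every pupil there. The share of pupils whose answers disclose is not given, so I assume a range of 2% to 10%, independent between pupils. With the target of 30 per school, the chance of at least one disclosure is:
- 1 − 0.98^30 = 45%
- 1 − 0.90^30 = 96%

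Colombia enrolled 160 in a planned eight schools, about 20 each. There the same range gives 1 − 0.98^20 = 33% to 1 − 0.90^20 = 88%. If the active-only set is visible to the assessor on the form, the first interview in a school is enough.

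**Step 5. Reach.** The masked sites hold 160 + 229 = 389 of 628 adolescents (62%, Table 4). The other 239 are in South Africa, where the assessors are not masked.

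**The case against.** The strongest reply is that much of the mechanism is inferred. The article does not say who asks the contamination items, in what mode, or where they fall in the session. It cites a standard operating procedure on preventing and assessing unmasking, and it places the full questionnaires in supplementary files; neither is shown here. Some questions at these sites may be self-completed, and these could include the contamination items or the PHQ-A and GAD-7 items. A team that separated its qualitative interviewers for this reason may have dealt with the point. All of this stands, and it is why the point is conditional.

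It does not remove the point. The article lists its masking measures (separate teams, separate offices, a guess at each assessment), and none covers these items. The timing of the guess is stated, and it is the less informative choice for a progression criterion.

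A reader might go further in three ways that the documents do not support:

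- **That the questionnaire breaks the trial's blind.** South African assessors have no blind to break. Elsewhere the wording necessarily separates only active from control.
- **That the masking criterion would be scored as failing.** Full active/control knowledge gives an expected 50%, which is amber, and under the article's definition amber allows progression with small adaptations. An expected red result needs the exact arm to be disclosed for more than a third of participants.
- **That nearly every pupil would be assessed by someone who knows the allocation.** That needs one assessor per school and disclosure by the first pupil seen. Staffing by school is not given.

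Participants may also mention their intervention at any point in a session, so not every correct guess can be put down to these items.

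**Conclusion.** The point holds for Colombia and Nepal, conditionally. As the article reads, the masked quantitative research assistants put to active-arm participants questions that reveal at least active versus control, and then record their guess. On that reading the masking row of Table 7 partly measures the questionnaire. Expected correct guesses rise from 25% to at most 50% if only active versus control is disclosed, and the green limit is reached once 40% of participants are disclosed. If answers also name the content, 13% is enough.

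This rests on equal arms, on chance guessing where nothing is disclosed, and on the inference about who asks and in what order. The standard operating procedure or the supplementary questionnaires could overturn that inference. Whether PHQ-A and GAD-7 ratings are affected is less certain, because those items may be self-completed. The remedy is cheap and a progression criterion depends on it, so the plan should be changed or clarified.

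**What to change.** At the masked sites:

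1. State who administers the contamination items and in what mode. Make them self-completed on the tablet, unseen by the assessor and placed after all outcome measures. Self-completion is already allowed there for some questions.
2. Record the assessor's guess after the last outcome measure and before the contamination block opens.
3. Score the Table 7 masking row on that guess. Moving the guess alone is not enough: it protects only a reading made before any disclosure in that school, since what is learned at T1 carries to later pupils and visits. Steps 1 and 2 belong together.
4. For visits already completed with interviewer-administered items, report guesses by visit and site and state this limitation. Recruitment ended in June 2024 and the last visit is 18 months after baseline, so this may be all that can still be done in the pilot.
5. Carry the revised order into the full trial.

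The cost is a reordering of the electronic form and a line in the masking procedure. The downside is slightly more missing contamination data among participants with low literacy.

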#### Data Safety Management Board

A Data Safety Management Board (DSMB) was established prior to the start of the pilot trial for the duration of the study, with a Charter that defines its role and terms of reference. It provides oversight on adverse events (AE, including Severe Adverse Events (SAE)) and safety protocols for the trial, to determine if interim analyses should be undertaken, and to make decisions as to the continuation of the trial in case of severe adverse events. The DSMB consists of four members, one expert from each site, and an independent statistician. The DSMB meets every 3 months for the duration of the trial. Each report of an (S)AE is sent to the DSMB, who ascertains whether the SAE is a result of participating in the trial, and whether the adequate response has been taken. The DSMB has the mandate to recommend stopping the study if it is determined that the risks of the study outweigh the benefits.

#### Data collection for qualitative interviews

Trained research assistants will conduct the qualitative interviews (within 4 weeks from terminating the intervention), independent from the team conducting quantitative assessments, given that intervention allocation of families would be revealed in these interviews. Semi-structured interviews (either individual or focus group discussions) will follow semi-structured guides, with topics exploring the perceived acceptability, feasibility and impact of the ALIVE intervention in each site, including facilitators and barriers to implementing the ALIVE interventions and completing the assessments, as well as recommendations for improvements. The interviews will be conducted in Spanish (Colombia), Nepali (Nepal) and English, isiXhosa or Afrikaans (South Africa); they should last approximately 30 min. The interviews will take place in the partner organisations’ offices or participants’ homes or in another private location of their choice or remotely. The brief interviews will be audio-recorded for transcription and translation purposes.

#### Training of research assistants

All research assistants conducting the assessments and qualitative interviews have experience in working among urban poor individuals. They will receive training lasting on average 3–6 days, reviewing general interview techniques, administering the instruments, and ethical research practice emphasising responding to participant distress. Following the training, research staff will have 2 weeks of practising assessments and interview role plays until the start of the trial. Research assistants will also be trained in the Adverse Events Reporting Mechanism, which guides the process of reporting and supporting/referral in case of any adverse events (see below).

#### Compensation of respondents

Each participant will receive supermarket vouchers or tokens of a maximum value of GBP 4 (Colombia), GBP 3 (Nepal) and GBP 8 (South Africa) after each screening/assessment or interview. A small reimbursement for transportation costs will also be provided when assessments, sessions or interviews take place outside of school or place of work, or outside of school-going/working hours (to a maximum value of GBP 7 (Nepal), GBP 2 (Colombia) and GBP 10 (South Africa) per participant per round trip). Refreshments will be provided during all assessment sessions, for adolescents and caregivers.

#### Adolescent Advisory Groups

Throughout the preparation for, and implementation of, the cRCT Adolescent Advisory Groups (AAGs) that have been established in each of the three countries as part of ALIVE, will provide inputs on the content of the quantitative and qualitative research instruments, as well as on the intervention content and delivery methods. Using participatory exercises, recurrent AAG meetings will pilot-test translations of instruments to advice on concerns of acceptability (e.g. wearing HRV devices, acceptable duration of assessments) and will review and advice intervention activities (e.g. type of physical activities, use of terminology). Furthermore, AAGs will be asked advice about measures we should put in place to reduce any negative influences of taking part in the interventions and study.

### Data analysis

#### Analyses of criteria for progression to full trial

The primary analyses for this pilot cRCT concern the assessment of a priori defined criteria that will be used for decision making for progression from pilot trial to an adequately powered trial. These criteria will be scored using a “red” (study cannot progress “as-is” but will require major adaptations to content or procedure), “amber” (progression can happen, but small adaptations should be considered to improve content of procedure) and “green” scoring (progression can happen without any adaptations). The criteria are listed in Table 7 and pertain to the feasibility of randomisation, data collection, masking and retention, as well as fidelity and adherence to ALIVE interventions, (severe) adverse events and safety of the cash transfers.

**Table 7 Tab7:** Criteria for progression to full trial

Criteria item	Indicator/measure	Alternative traffic light system		
		Red	Amber	Green
**Feasibility of the study procedures**				
Feasibility of randomisation	Difference in participant recruitment rate between arms	1. > 60% participants agree to be (i) re-screened to determine eligibility for the pilot, or (ii) enrolled into the pilot (when second screening for pilot does not take place) 2. > 30% difference in recruitment rate between arms	1. > 60% participants agree to be (i) re-screened to determine eligibility for the pilot, or (ii) enrolled into the pilot (when second screening for pilot does not take place) 2. 20–30% difference in recruitment rate between arms	1. > 60% participants agree to be (i) re-screened to determine eligibility for the pilot, or (ii) enrolled into the pilot (when second screening for pilot does not take place) 2. < 20% difference in recruitment rate between arms
Feasibility of masking research assistants	Self-report questions at the end of each assessment	> 50% guess correct arm	35–50% guess correct arm	< 35% guess correct arm
Feasibility of data collection	Proportion of missing items on the GAD-7 and PHQ-A items at 18 month follow-up	> 20% missing	10–20% missing	< 10% missing
Feasibility of retention	Proportion of recruited adolescents lost to follow-up (LTFU) at 18-month follow-up	> 30% LTFU	20–30% LTFU	< 20% LTFU

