**Methods:**

The study takes place in Bogotá (Colombia), Kathmandu (Nepal) and Cape Town (South Africa). The pilot cRCT has four arms: (i) self-regulation intervention, (ii) economic intervention, (iii) combined (self-regulation + economic) intervention, and (iv) control group (care as usual). Interventions consist of 20 weekly group sessions with adolescents, and 6 monthly group sessions with their caregivers. The self-regulation intervention for adolescents includes psychological activities (mindfulness breathing, problem solving, biofeedback and goal setting) and a physical activity. The economic intervention includes three dimensions (financial training, negotiation training, education information) and a monthly cash transfer. In each site, the aim was to recruit 240 adolescents and their caregivers across eight schools (clusters), with two schools randomised to each arm. Adolescents residing in areas at risk of multidimensional poverty and who had symptoms of depression or anxiety, but who did not meet thresholds indicating depression and anxiety disorders, were considered for enrolment. Recruitment into the study is complete: a total of 628 adolescents and 536 caregivers were enrolled. Participants will be assessed four times: at enrolment, post-intervention and at 12 and 18 months post-enrolment. Primary outcomes include feasibility and acceptability criteria for study and intervention delivery procedures (i.e. randomisation, masking, recruitment, retention, missingness, fidelity, attendance, adverse events) defined as traffic light criteria to assess progression to an adequately powered trial. Secondary outcomes include self-report instruments, physiological measures and neuropsychological tasks.

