### Objectives

The primary aim of this study is to evaluate the feasibility and acceptability of an intervention that combines an economic intervention with a self-regulation intervention among adolescents living in urban poverty in Bogotá (Colombia), Kathmandu (Nepal) and Cape Town (South Africa). This will be done by assessing the following criteria (which have been defined as progression to full trial criteria): (1) fidelity across intervention arms; (2) participants attending sufficient intervention sessions; (3) reported adverse events across intervention arms compared to control arm; (4) reported negative experiences related to cash transfers, as well as qualitative perspectives on acceptability of interventions; (5) baseline differences in demographic variables across arms for adequacy of randomisation; (6) adequacy of masking; (7) missing values on outcome instruments; (8) loss to follow-up across timepoints. Furthermore, we aim to evaluate the sensitivity to change on study participants’ clinical and non-clinical outcomes. The study is part of the ‘Improving Adolescent mentaL health by reducing the Impact of poVErty (ALIVE)’ project, which has been introduced elsewhere [12].

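### In the progression table, the 60% agreement condition is identical under red, amber and green, so agreement of 60% or less has no colour and cannot be scored red

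*Protocol article*

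**What the plan says.** The Data analysis section of the protocol article states that the primary analyses concern progression criteria set in advance and scored by colour. Red means the study cannot go forward unchanged and needs major adaptation. Amber allows progression with small adaptations, and green allows it with none. The abstract likewise describes the primary outcomes as "defined as traffic light criteria to assess progression to an adequately powered trial".

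In Table 7, the row on feasibility of randomisation names one indicator: "Difference in participant recruitment rate between arms". Each colour cell then has two numbered parts.

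- Part 1, the same in all three cells: "> 60% participants agree to be (i) re-screened to determine eligibility for the pilot", with agreement to enrolment as the alternative where no second screening takes place.
- Part 2, red: "2. > 30% difference in recruitment rate between arms".
- Part 2, amber: "2. 20–30% difference in recruitment rate between arms".
- Part 2, green: "2. < 20% difference in recruitment rate between arms".

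The Objectives section lists the criteria that define progression. Its item (5) is "baseline differences in demographic variables across arms for adequacy of randomisation".

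**The concern.** A traffic-light rule should give every possible result exactly one colour, with worse results moving towards red. Part 1 does neither. A condition common to all three colours cannot distinguish them, and a result that fails it falls outside the table. The direction is also wrong in the red cell, where good agreement is a requirement for the worst score.

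What is at stake is the scoring of one row of the primary outcome. If agreement were 60% or less, the team would have to decide after seeing the data whether to call the row red, leave it blank, or score it on the between-arm difference alone. Setting criteria in advance is meant to prevent that choice. The same section makes the sample size work for the powered trial conditional on all progression criteria being met, so an unscored row would leave that condition open.

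A secondary mismatch sits beside this. Objective (5) says adequacy of randomisation is judged by baseline demographic differences, whereas the table's randomisation row looks at agreement and recruitment rates. No row of Table 7 measures baseline balance.

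**Working it through.** No power or sample size calculation is involved. The check is whether the printed rule covers all outcomes.

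**Inputs (Table 7, feasibility of randomisation).** Let A be the percentage agreeing and D the between-arm difference in recruitment rate, in per cent.

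**Rule as printed**, reading the two numbered parts of each cell as jointly required:

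- Red: A > 60 and D > 30
- Amber: A > 60 and 20 ≤ D ≤ 30
- Green: A > 60 and D < 20

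**Step 1: spot values.**

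| A | D = 5 | D = 25 | D = 45 |
|---|---|---|---|
| 40 | none | none | none |
| 60 | none | none | none |
| 61 | green | amber | red |
| 80 | green | amber | red |
| 95 | green | amber | red |

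The rows for 61, 80 and 95 are the same: above 60, the colour depends on D alone. The rows for 40 and 60 are empty.

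**Step 2: full coverage.** Take whole numbers 0 to 100 for both A and D, which gives 101 × 101 = 10,201 combinations.

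- A ≤ 60: 61 × 101 = 6,161 combinations, all without a colour.
- A > 60: 40 × 101 = 4,040 combinations, each with exactly one colour: green 40 × 20 = 800, amber 40 × 11 = 440, red 40 × 70 = 2,800.

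The uncoloured region is exactly A ≤ 60. The counts show where the gap lies; they are not probabilities that it will be met.

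**Step 3: the same check on the corrected rule** (red: A ≤ 60 or D > 30; amber and green unchanged). Red becomes 6,161 + 2,800 = 8,961, with amber 440 and green 800. The sum is 8,961 + 440 + 800 = 10,201, so every combination has one colour and no result that already had a colour changes it.

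**Step 4: unit of the difference.** The table does not say whether D is in percentage points or relative. Take 80% in one arm and 60% in another as an illustration. The difference is 80 − 60 = 20 percentage points, which is amber. Relative to the lower arm it is 20/60 = 33%, which is red. The colour can therefore depend on an unstated convention.

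**Step 5: comparison with other rows.** Masking, missing items, retention, fidelity, attendance, adverse events and cash-transfer safety all have bands that change from red to green. Retention, for example, uses loss above 30%, 20–30% and below 20%. Part 1 of the randomisation row is the only graded entry that does not change.

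**The case against.** The best defence is that part 1 is a common precondition. The row is about randomisation, its named indicator is the between-arm difference, and that difference is graded coherently. Because amber and green both require more than 60% agreement, low agreement cannot obtain either colour that permits progression. On this view only an explicit red label is missing.

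Much of that stands. The row does separate the colours through part 2, and low agreement is not rewarded under the rule as printed. A reader might infer that the row lets a poorly recruiting trial proceed, for instance that 40% agreement with a 5% difference scores green. That follows only if part 1 is ignored, which the table does not say to do. A reader might also think that 95% agreement with a 31% difference is red because agreement was high; it is red because of the difference, as intended.

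The precondition reading does not remove the defect, however. The table does not call part 1 a precondition, does not say what follows when it fails, and places it inside red, where a condition for proceeding has no function. A text-extraction fault is an unlikely explanation, since each cell has its own version of part 2. Nor is this a detail left to a fuller document: the article prints the cut-offs itself.

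**Conclusion.** The point holds as a mis-stated threshold in one of the eight rows of the progression table. Part 1 never changes the colour, agreement of 60% or less is unscorable, and the red cell requires the opposite of what it should. It should be fixed. It is not graver than that, because low agreement already fails amber and green and the remaining rule is sound. The conclusion assumes that the two numbered parts of a cell must both be met.

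A reader might go further and cite enrolment against target: Colombia 160/240 = 66.7%, Nepal 229/240 = 95.4%, South Africa 239/240 = 99.6%. The documents do not support using this here. Those figures are enrolled over planned, whereas part 1 concerns agreement among those asked. The number asked is not given, so no agreement rate can be computed and no site is shown to be at or below 60%. Repeat screening, caregiver enrolment and the exclusion criteria can also reduce enrolment without anyone declining.

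The mismatch between Objective (5) and the table is real but secondary, and does not raise the weight of the threshold point.

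**What to change.** In the randomisation row of Table 7:

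- Red: 60% or less agree, or a between-arm difference above 30 percentage points.
- Amber: more than 60% agree and a difference of 20–30 percentage points.
- Green: more than 60% agree and a difference below 20 percentage points.
- Indicator column: add the agreement rate alongside the between-arm difference.

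These use the protocol's own cut-offs; only the red cell changes in substance, and the unit is made explicit. Separately, bring Objective (5) and the table into line: let the objective refer to the agreement and recruitment rates that the row measures, and report baseline demographic balance descriptively. With two schools per arm in each country, some imbalance is expected by chance and would say little about whether randomisation was done properly.

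The cost is the wording of one row and one objective, with no new data. The small downside is timing. Recruitment ended in June 2024, so the agreement data already exist and the change cannot be presented as part of the criteria set in advance. It should be dated and disclosed as made after recruitment, and made before scoring if scoring has not begun; if it has, the change should be declared post hoc.
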